##### Global Deterioration Scale

2.10.3.4

The GDS assesses the severity of cognitive decline over 7 stages, that is, stage 1 shows no cognitive impairment, stage 2 shows very mild cognitive impairment, stage 3 shows mild cognitive impairment, stage 4 shows moderate cognitive impairment, stage 5 shows moderate severe cognitive impairment, stage 6 shows severe cognitive impairment, stage 7 shows very severe cognitive impairment.^[21]^

##### Activity of Daily Life

2.10.3.5

The ADL assesses 20 domains of activities, which includes physical self-maintenance scale and instrumental activities daily of life. Physical self-maintenance scale includes 6 basic activities: toilet, feed, dressing, grooming, physical moving, and bath, and instrumental activities daily of life includes 8 instrumental activities: using telephone, going shopping, preparing food, doing housework, doing the laundry, transportation, taking medicine, ability to handle finances.^[22]^ The scale is divided into 4 grades: 1 = self-care; 2 = have some difficulties; 3 = need help; 4 = unable to complete. The total score ranged from 20 to 80. If the score of single item is 1, it is normal; if the score of single item is 2 to 4, it is functional decline. If the total score = 20 points, it indicates absolutely normal; if the total score is >20, it indicates different levels of functional decline. The higher the score, the worse the ability to live.

##### Alzheimer Disease Assessment Scale-Cognitive Section

2.10.3.6

The ADAS-cog includes 12 cognitive domains, containing recall of word, recognizing word, constructional practice, orientation, denominating, commands, ideational practice, recall test commands, verbal ability, looking for words, comprehension, and concentration. The total scores ranges from 0 to 75. The higher the score, the poorer the cognitive impairment.^[23,24]^

##### Brain magnetic resonance imaging

2.10.3.7

MRI structural imaging can show different brain lesions, which is helpful for the etiological diagnosis and monitoring of the progress of MCI. The most common local brain changes in aMCI are atrophy of the hippocampus and the entorhinal cortex.^[25]^ Besides, atrophy of hippocampus and entorhinal cortex are reliable indicators of the transformation of aMCI to AD.^[26,27]^ Other brain changes on MRI in patients with MCI include decreased cortical gray matter, enlarged ventricles, and increased white matter high signal intensity.^[27]^

##### Brain functional magnetic resonance imaging

2.10.3.8

Cerebral activation can be researched by Blood-Oxygen-Level-Dependent signal of fMRI. Blood-Oxygen-Level-Dependent signal would make differences when there are pathological changes associated with neurodegenerative disease.^[28–30]^ Default mode network is a focus network for the study of cognitive function by using resting-state functional MRI. It includes the posterior cingulate/anterior cuneiform lobe, medial prefrontal cortex, hippocampus, angular gyrus, and ventral anterior cingulate gyrus,^[31]^ which are related to cognitive function, executive function, and situational memory. resting-state functional MRI in aMCI patients is mainly manifested as the gradual weakening of functional connections in the default mode network of brain regions, such as hippocampus and medial prefrontal lobe.^[32]^

#### Event-related potential P300

2.10.4

ERP are electric signals from the brain, which relate to miscellaneous cognitive function, like selective concentration, memory, or discretion.^[33–35]^ Component of P300 is the research hotspot of ERP and the numerous clinical P300 studies^[36–42]^ show that the component can be used as an index of cognitive function. The prolonged latency and declining amplitude of P300 shows cognitive impairment.

#### Adverse events of acupuncture

2.10.5

The incidence rate of acupuncture's AEs during treatment will be counted. Clinical symptoms and related laboratory examination results of acupuncture's AEs will be recorded to judge their grades. Follow-up visits after AEs will be recorded.

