#### Clinical outcomes

2.10.1

We will evaluate the neuropsychological assessment scale (Mini-mental State Examination [MMSE], Montreal cognitive assessment [MoCA], CDR, Delayed Story Recall, GDS, ADL, Alzheimer Disease Assessment Scale-Cognitive Section [ADAS-cog]), brain cranial magnetic resonance imaging (MRI) and brain functional cranial fMRI, latency and amplitude of event-related potential (ERP) P300 before and after treatment. This incidence rate of acupuncture AEs will be counted. We will evaluate neuropsychological assessment scale (MMSE, MoCA, ADAS-cog) at 3 months and 6 months after treatment.

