### Safety

2.11

We will evaluate vital signs, blood routine, urine routine, liver and kidney function, coagulation function, electrocardiogram, and clinical symptoms and related laboratory examination results of acupuncture's AEs at pre-therapy and posttherapy.

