### Blinding

2.15

Patients will be notified that they will be received acupuncture treatment or acupuncture-like simulation treatment, which is randomly allocated. And they will be required to close their eyes during treatment. Only the acupuncturists will be aware of the detailed grouping. Subjects and other investigators (like data analysts, outcome evaluators, and statisticians) will not know group assignments. All investigators will receive trial training before the study starts to ensure the success of the implementation of blind method.

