### Safety and adverse events

2.17

If participants are considered to have undesirable effect after acupuncture treatment, they should discontinue treatment and tell acupuncturists. Acupuncturists will diagnose and cure the AE, and other investigator will contact them to fill in the AE form and AE record log. AEs may occur during acupuncture, such as fainting, hematoma, bent needle, stuck needle, broken needle, infection, etc. If any relevant AE occurs during the study, it will be dealt with immediately.

Participants and acupuncturists should report all of the AEs (include all discomfort, symptoms, or illness occurring during the study). All detailed information of AEs (include occurrence time, symptoms, duration, severity, treatment measures, and duration) will be reported in the case report forms (CRFs). In case of serious AE, it will be reported to the lead unit and the state administration of traditional Chinese medicine within 24 hours. One week after symptomatic treatment, follow-up will be conducted through outpatient service, telephone, or visit. We will analyze the impact of all AEs after this trial finishes.

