### Statistical analysis

2.19

The statistical tests involved in this study will include unilateral and bilateral tests with a significance level of alpha = 0.05. Statistical analysis will be completed by SPSS 22.0 software (International Business Machines Corp., Armonk NY).

Effect analysis will involve a population consisting of per-protocol subject analysis and intention-to-treat analysis. We will adopt a repeated measures design approach to compare the treatment outcomes (MoCA, MMSE, and ADAS-cog) over time between 2 groups. The model will be built to distinguish the intervention effect and the time effect. Among-group differences at each assess time point will be further tested by student *t* test. Categorical variables, containing categorical baseline variables and incidence of AEs, will be analyzed by a chi-square (χ^2^) or Fisher exact test.

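### The adverse-event outcome is defined two ways (AEs of acupuncture, or all AEs), and the narrower count has no arm-neutral meaning and rests on diagnosis by the only unblinded staff

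*Protocol article*

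**What the plan says.** Three outcome sections of the protocol article use a restricted term. Clinical outcomes (2.10.1) states "This incidence rate of acupuncture AEs will be counted". Adverse events of acupuncture (2.10.5) states "The incidence rate of acupuncture's AEs during treatment will be counted" and also limits grading to those events. Safety (2.11) opens with measures that need no attribution, "We will evaluate vital signs, blood routine, urine routine, liver and kidney function, coagulation function, electrocardiogram, and clinical symptoms", but ties the clinical symptoms to the AEs of acupuncture.

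Two later sections are wider. Safety and adverse events (2.17) says "Participants and acupuncturists should report all of the AEs (include all discomfort, symptoms, or illness occurring during the study" and adds "We will analyze the impact of all AEs after this trial finishes". Statistical analysis (2.19) says "Categorical variables, containing categorical baseline variables and incidence of AEs, will be analyzed by a chi-square" or Fisher exact test, with no limit to acupuncture AEs.

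On roles, 2.17 says "Acupuncturists will diagnose and cure the AE, and other investigator will contact them to fill in the AE form and AE record log", and Blinding (2.15) says "Only the acupuncturists will be aware of the detailed grouping". Section 2.15 also states that subjects and the other investigators do not know the assignment.

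**The concern.** Safety is a stated aim of this pilot and is meant to inform a larger trial. Under 2.17 an event is recorded whatever its cause. Under 2.10.1 and 2.10.5 it reaches the named outcome only if it is an AE of acupuncture. The article does not say what that means in the sham arm, where the needle touches the skin without piercing it, or who decides.

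The diagnosis on which any such decision would draw comes from staff who know the arm. For an unspecific complaint such as dizziness or headache, an acupuncturist who knows that neither needle nor current was applied has little reason to connect it with acupuncture. One who delivered real needling may connect it readily, or may be reluctant to blame the technique. Quality control (2.21) keeps efficacy evaluators out of treatment but states no matching safeguard for AEs. If the restricted count is the one tested, the comparison mixes event rates with judgements made in knowledge of the arm.

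**Working it through.** **1. The plan's own figures.** The article gives no AE rate and no AE power. Its sample size (13 per group before loss, 25 per group planned) was set on MoCA and does not bear on this point. Only n = 25 per arm is used below.

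**2. The sections side by side.**

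| Section | Which AEs | Restricted to acupuncture? |
|---|---|---|
| 2.10.1 | incidence counted | yes |
| 2.10.5 | incidence counted, during treatment | yes |
| 2.11 | symptoms and laboratory results of AEs (with vital signs, laboratory tests, ECG) | yes, for the AE part |
| Table 1 | AEs at baseline, 12 weeks, 3 and 6 months | no |
| 2.17 | all AEs reported; impact of all AEs analysed | no |
| 2.19 | incidence tested between arms | no |

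The only AE incidence defined as an outcome is the restricted one. The only AE incidence assigned a test is unrestricted. Nothing says whether they are the same variable.

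**3. Does the restricted term mean the same in both arms?** Section 2.17 names six examples. Bent, stuck and broken needle and haematoma can hardly occur without insertion. Infection is less likely without it but possible, since the device base is stuck to the skin in both arms. Fainting can occur in either. The list is open-ended.

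**4. How attribution moves the count (assumed figures).** Reported rate in an arm = true rate × fraction attributed to acupuncture. Assume unspecific AEs in 30% of both arms, that is 0.30 × 25 = 7.5 participants each.

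- 60% attributed in the real arm, 10% in sham: 0.30 × 0.60 = 18% and 0.30 × 0.10 = 3%.
- 10% attributed in both: 3% and 3%, a tenfold under-count with no difference between arms.
- In general the spurious difference is 0.30 × (real-arm fraction − sham fraction). It is 0 when the fractions are equal and at most 30 percentage points in either direction.

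In patients, 18% v 3% is 4.5 v 0.75 of 25. Even 5 v 1 gives a two-sided Fisher p of about 0.19.

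**5. How the choice of numerator changes the test (assumed rates, two-sided Fisher, 25 v 25).** With 0 of 25 in sham, p = 0.110 for 4 of 25, 0.0502 for 5 of 25 and 0.022 for 6 of 25 in the acupuncture arm. The chance of p ≤ 0.05 is:

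| Needle-related events only | Chance | With 10% background added to both arms | Chance |
|---|---|---|---|
| 20% v 0% | 38% | 30% v 10% | 31% |
| 30% v 0% | 81% | 40% v 10% | 59% |

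The definition changes what the test can show. Under neither definition is the result settled beforehand.

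**The case against.** A reader might infer that only acupuncture AEs will be counted and that the comparison is therefore fixed by construction or by knowledge of the arm. The documents do not support that. Section 2.17 says the impact of all AEs will be analysed, 2.19 tests AE incidence without restriction, and 2.11 adds measures that need no attribution. Participants, who are blinded, report AEs too, and a second investigator fills in the form and log. Section 2.17 gives the acupuncturists diagnosis and treatment. It does not say that they judge relatedness. The list of examples is open and includes fainting. An excess of haematomas or stuck needles under real needling would be a true effect of the treatment, not a bias. The restricted phrase might also mean simply AEs arising during study treatment, and detailed causality rules may stand in the full protocol.

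All of this stands against the stronger reading. It does not remove the inconsistency. The analysis of the impact of all AEs names no measure and no comparison by arm, the measures in 2.11 are not AE counts, and a blinded recorder who transcribes an unblinded diagnosis does not undo its effect. That the restricted phrase can be read in more than one way is itself part of the problem. Leaving causality rules to a fuller document is normal. Printing two different numerators for one outcome is an inconsistency in the article itself.

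**Conclusion.** The point holds as an inconsistency with a risk of bias. The AE outcome is restricted in 2.10.1, 2.10.5 and 2.11 and unrestricted in 2.17 and 2.19. The restricted version has no arm-neutral definition against a non-penetrating sham, and it rests on diagnosis by the only unblinded staff. A between-arm comparison on that version would be open to ascertainment bias in either direction.

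The size of that bias cannot be derived, because the documents give neither AE rates nor attribution rates. The percentages above are illustrations on assumed values. They show that the choice of numerator matters, not that a false result is likely: the assumed 18% v 3% would usually not be significant with 25 per arm. No AE criterion enters the progression rules in Table 3, so the consequence lies in the safety estimate carried forward to the larger trial. This is a change that should be made because it is cheap, not a fault that invalidates the design.

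**What to change.** In 2.10.1, 2.10.5, 2.11 and 2.19, make the compared outcome the proportion of participants with at least one AE of any cause, by arm, taken from the all-AE record that 2.17 already requires. State the counting window with it, since 2.10.5 covers the treatment period while Table 1 lists AEs to 6 months.

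In 2.17, have the investigator who completes the AE form, and who is blind to arm under 2.15, assign relatedness and grade from facts reported by the acupuncturist. Report acupuncture-related and needle-specific events separately as description. Needle-specific events will often reveal the arm to the assessor, which is a further reason to keep them apart from the main comparison.

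The cost is wording in five sections and one more AE table. No new data or staff are needed, because 2.17 already provides both. The downside is a higher and less specific AE rate: in the illustration, a 10% background lowers the chance of detecting a 30-point excess from 81% to 59%. The separate description of needle-related events keeps that information visible.

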### Safety

2.11

We will evaluate vital signs, blood routine, urine routine, liver and kidney function, coagulation function, electrocardiogram, and clinical symptoms and related laboratory examination results of acupuncture's AEs at pre-therapy and posttherapy.

### Feasibility

2.12

In order to evaluate the feasibility of carrying out RCTs with large samples in the next stage, we set the following indicators in this pilot trial. The feasibility outcomes are demonstrated in Table 3.

**Table 3 T3:** Feasibility outcomes.

Feasibility outcomes	Evaluation criteria
1. Proportion of participants who completed the required 12-week acupuncture treatment and cognitive rehabilitation training program	If ≥80% participants completed, proceed; if 50%–80% participants completed, modify protocol; if <50% participants completed, do not proceed.
2. Proportion of participants who completed a 12-week aerobic exercise program	If ≥80% participants completed, proceed; if <80% participants completed, modify protocol.
3. Rate of drop-out during treatment	If rate of drop-out ≤20%, proceed; if rate of drop-out is 20%–50%, modify protocol; if rate of drop-out <50%, do not proceed.
4. Response rate	Response rate of subjects to the collected indicators will be evaluated at pre-therapy, posttherapy, 3 months and 6 months after treatment.
5. Blinding test	All the participants will be tested for the success of blinding after the final treatment session. They will be asked to judge whether they have received real acupuncture or sham acupuncture.
6. Satisfaction	Participants’ satisfaction with the intervention will be ranked on a 5-point scale, each point is very satisfied, satisfied, neutral, dissatisfied, and very dissatisfied.
7. Average number of eligible subjects recruited in each center per month	Each center separately counts the number of eligible participants.
8. Enrollment rate	Proportion of participants who were last included in the study among all eligible participants.

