**Method::**

We designed a pilot multicenter, randomized, parallel controlled trial. This trial aims to test the feasibility of carrying out a large-sample clinical trial. In this trial, 50 eligible patients with aMCI will be included and allocated to acupuncture group (n = 25) or sham acupuncture group (n = 25) at random. Subjects will accept treatment 2 times a week for 12 weeks continuously, with a total of 24 treatment sessions. We will select 6 acupoints (GV20, GV14, bilateral BL18, bilateral BL23). For the clinical outcomes, the primary outcome is Montreal cognitive assessment, which will be assessed from baseline to the end of this trial. And the secondary outcomes are Mini-mental State Examination, Delayed Story Recall, Clinical Dementia Rating scale, Global Deterioration Scale, Activity of Daily Life, Alzheimer Disease Assessment Scale-Cognitive Section, brain magnetic resonance imaging, brain functional magnetic resonance imaging, and event-related potential P300, which will be assessed before and after treatment. In addition, we will assess the safety outcomes from baseline to the end of this trial and feasibility outcome after treatment. We will evaluate neuropsychological assessment scale (Montreal cognitive assessment, Mini-mental State Examination, Alzheimer Disease Assessment Scale-Cognitive Section) at 3 months and 6 months after treatment.

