### Sample size

2.13

Based on the RCT report published by Jiang et al^[43]^ in 2016, the sample size was estimated with MoCA as the main outcome. After 12 weeks of treatment, the difference of MoCA between pre-therapy and posttherapy in the conventional rehabilitation group (without acupuncture) was 2.83 ± 1.13, and that of MoCA between pre-therapy and posttherapy in acupuncture group was 1.33 ± 1.20. The test level was set at *α* = 0.05 and *β* = 0.1. By comparing the differences between 2 independent samples, PASS 2008 software was used to calculate that the required sample size of each group was 13 cases, and 26 cases in both groups.

To sum up, considering that the follow-up loss rate is 20%, the sample size should be 26/(1 – 0.2) = 33 cases. Considering that we have enough research capacity to fulfill the expected research tasks, we intend to expand the sample size to a total of 50 cases, 25 cases in each group.

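### In Table 3, exactly 80% completed (item 1) and exactly 20% drop-out (item 3) each fall in both the proceed band and the modify band

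*Protocol article*

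**What the plan says.** The abstract gives the purpose: "This trial aims to test the feasibility of carrying out a large-sample clinical trial". Section 2.12 says the indicators in Table 3 serve that purpose, and three of them carry cut-offs.

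- Item 1, completion of the acupuncture and cognitive training programme: "If ≥80% participants completed, proceed; if 50%–80% participants completed, modify protocol; if <50% participants completed, do not proceed".
- Item 2, completion of the aerobic exercise programme: "If ≥80% participants completed, proceed; if <80% participants completed, modify protocol".
- Item 3, drop-out during treatment: "If rate of drop-out ≤20%, proceed; if rate of drop-out is 20%–50%, modify protocol; if rate of drop-out <50%, do not proceed".

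Section 2.13 gives the planned number: "we intend to expand the sample size to a total of 50 cases, 25 cases in each group". The only loss rate it states is in the step before that: "considering that the follow-up loss rate is 20%, the sample size should be 26/(1 – 0.2) = 33 cases".

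**The concern.** A progression rule is useful because it ties each possible result to one action before the data are seen. In items 1 and 3 the proceed band includes its end point by an explicit inequality, and the modify band is written as a range that starts or ends at that same point. One result therefore carries two actions. If the pilot lands there, the choice between going ahead unchanged and revising the protocol is made after the result is known. That is what a pre-stated rule is meant to prevent, and here the decision is a stated aim of the pilot.

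**Working it through.** **1. The bands side by side.**

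| Item | Proceed | Modify | Do not proceed | Verdicts at the boundary |
|---|---|---|---|---|
| 1 (completed) | ≥80% | 50%–80% | <50% | at 80%: proceed and modify |
| 2 (completed) | ≥80% | <80% | none | at 80%: proceed only |
| 3 (dropped out) | ≤20% | 20%–50% | <50% as printed | at 20%: proceed, modify and, as printed, do not proceed |

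Item 2 has no overlap. The third verdict in item 3 comes from its stop band, whose inequality appears reversed. That is a separate fault. If its direction were changed, the shared point at 20% would remain.

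**2. Can the shared point occur?** An exact 80% needs 0.8 × N to be a whole number, so N must be a multiple of 5. The planned N = 50 (2.13) is one: 0.8 × 50 = 40 completers and 0.2 × 50 = 10 drop-outs. If the final denominator were not a multiple of 5, the shared point could not be hit.

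**3. Where the plan's own 20% comes from.** Section 2.13 uses it once, to inflate the total: 26 / (1 − 0.2) = 32.5, rounded up to 33. This reproduces the stated figure. The 20% is called a follow-up loss rate, and follow-up runs to 6 months after treatment ends (2.1). Item 3 counts drop-out during treatment, and item 1 counts completion of two programmes. The article gives no expected value for either.

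**4. How often the exact count would arise.** Let X be the number of completers among 50, binomial with true completion rate p. Then P(X = 40) = C(50, 40) × p^40 × (1 − p)^10.

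| True completion rate p (assumed) | P(X = 40) | P(X ≥ 40) | P(X ≥ 41) |
|---|---|---|---|
| 70% | 0.039 | 0.079 | 0.040 |
| 75% | 0.099 | 0.262 | 0.164 |
| 80% | 0.140 | 0.584 | 0.444 |
| 85% | 0.089 | 0.880 | 0.791 |
| 90% | 0.015 | 0.991 | 0.975 |

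For item 3, read p as one minus the drop-out rate; the figures are the same. The two right-hand columns are the chance of proceed with the boundary assigned to proceed and to modify respectively. They differ by P(X = 40), for example 0.584 − 0.444 = 0.140. That difference is all the ambiguous wording controls. It is largest among these rates at 80% and falls to 0.015 at 90%.

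**The case against.** The best defence is that the table is readable as it stands. The proceed bands carry explicit signs, the middle bands are ordinary range shorthand, and item 2 shows the intended convention. Read from left to right, exactly 80% completed and exactly 20% drop-out both give proceed. This limits the fault to a single point with a likely intended answer, and the neighbouring verdict is to modify, not to stop. It does not remove the fault: the table gives no order of precedence, and the exclusive form in item 2 is a reason to use it throughout.

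Three stronger readings are tempting, and the document does not support them.

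- A reader might infer that a pilot running exactly as planned would be told to proceed only about half the time, from the 0.444 and 0.584 at a true 80%. That treats the follow-up loss rate in 2.13 as a forecast of drop-out during treatment or of completion, which the article never does. If treatment drop-out were 15%, the chance of proceed on item 3 would be 0.88; at 10%, 0.99. If completion of both programmes were 75%, the chance on item 1 would be 0.26. A near-even chance also follows from any cut-off placed at the true rate: with the overlap settled in favour of proceed it is still 0.584.
- A reader might infer that 50 participants rest on MoCA power alone. Section 2.13 derives 33 from MoCA power and the loss allowance, then moves to 50 on grounds of research capacity.
- A reader might fault the article for not giving the precision of these rates, or for not saying how a result close to a cut-off is labelled. A condensed article may leave such detail to the full protocol or the analysis plan.

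**Conclusion.** The point holds as a minor drafting fault in a stated decision rule. In item 1 exactly 80%, and in item 3 exactly 20%, each carry more than one verdict, and with 50 participants both are attainable (40/50 and 10/50). The probability of landing on that count is 0.14 if the true rate is 80% completed or 20% dropped out, and between 0.015 and 0.099 at the other completion rates from 70% to 90% tabulated. These figures assume that all 50 participants form the denominator, that participants behave independently, and that the true rate is as supposed. The article supplies none of those true rates. The overlap is smaller in consequence than item 3's stop band, which as printed applies to every drop-out rate below 50% and leaves rates above 50% without a verdict.

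**What to change.** In Table 3, write the bands so that each result has one verdict, following item 2:

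- Item 1: proceed at ≥80%; modify at 50% to <80%; do not proceed at <50%.
- Item 3: proceed at ≤20%; modify at >20% to 50%.

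In the same edit, reconcile item 3's do-not-proceed band with its other two bands. Correcting only the 20% boundary would leave item 3 contradictory.

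The cost is a few characters in one table. Design, sample size, data collection and analysis do not change. The article says the trial is already under way, so the correction should be dated and made before the completion and drop-out rates are known.

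### All banded go/no-go criteria in Table 3 stop at week 12; retention at the 3- and 6-month MoCA visits is reported but has no preset threshold

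*Protocol article*

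**What the plan says.** Section 2.12 lists eight feasibility indicators in Table 3. Three carry numeric decision bands:

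- Item 1: "Proportion of participants who completed the required 12-week acupuncture treatment and cognitive rehabilitation training program".
- Item 2: "Proportion of participants who completed a 12-week aerobic exercise program".
- Item 3: "Rate of drop-out during treatment", with the favourable band "If rate of drop-out ≤20%, proceed" and a last band printed as "if rate of drop-out <50%, do not proceed".

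Item 4 is the only indicator that extends past treatment: "Response rate of subjects to the collected indicators will be evaluated at pre-therapy, posttherapy, 3 months and 6 months after treatment". It states no cut-off and no consequence. Items 5 to 8 (blinding, satisfaction, recruitment per centre, enrolment rate) have no bands either.

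On the outcome, the Abstract says that "the primary outcome is Montreal cognitive assessment, which will be assessed from baseline to the end of this trial". Table 1 and section 2.10.1 schedule MoCA at baseline, week 12, and 3 and 6 months after treatment. Section 2.19 puts MoCA into a repeated-measures comparison of the two groups. Section 2.13 sizes the trial on the 12-week MoCA change and then inflates the number, "considering that the follow-up loss rate is 20"%.

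**The concern.** The pilot exists to show whether a larger trial can be run. Two of the four scheduled MoCA assessments fall after treatment ends, and contact then drops from two sessions a week to two visits. Retention over that stretch is one of the things a pilot should test. The team chose to set bands for retention, but the bands end at week 12. Heavy loss at 3 or 6 months would appear in the report without triggering any action fixed in advance, so its weight would be settled after the data are seen. The larger trial could then be planned with follow-up visits that the pilot had shown to be hard to fill.

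**Working it through.** **The plan's own figure.** Inputs from section 2.13: mean changes 2.83 (SD 1.13) and 1.33 (SD 1.20), alpha 0.05, power 90%.

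- Difference: 2.83 − 1.33 = 1.50.
- Common variance: (1.13² + 1.20²)/2 = 1.358, so SD = 1.166.
- Two-sided normal approximation: n per group = 2 × (1.960 + 1.282)² × 1.358 / 1.50² = 12.7, rounded up to 13; total 26.
- Inflation: 26/(1 − 0.2) = 32.5, rounded up to 33; the plan then expands to 50.

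The stated 13, 26 and 33 reproduce. They rest on the 12-week change, so the 20% allowance belongs to that comparison.

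**Window of each retention-related criterion in Table 3.**

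| Item | Period covered | Numeric band |
|---|---|---|
| 1 Treatment and training completed | 12 weeks | yes |
| 2 Exercise completed | 12 weeks | yes |
| 3 Drop-out | treatment phase | yes |
| 4 Response rate | all visits to 6 months | none |

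No row combines a period beyond week 12 with a band.

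**What items 1 to 3 can miss.** Take 50 randomised. Read the last band of item 3 as above 50%, which is its evident intent, and assume that everyone still in the trial at week 12 completed treatment, training and exercise. Up to 10 of 50 may then be lost in treatment with items 1 to 3 all favourable. Let f be the loss among those remaining. The number with a 6-month MoCA is (50 − lost in treatment) × (1 − f). The article gives no separate follow-up loss rate, so every f is an assumption.

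| Lost in treatment | f | 6-month MoCA | Total loss | Items 1 to 3 | Same cut-offs applied at 6 months |
|---|---|---|---|---|---|
| 10 | 0% | 40 | 20% | proceed | proceed (80%) |
| 10 | 10% | 36 | 28% | proceed | modify (72%) |
| 10 | 20% | 32 | 36% | proceed | modify (64%) |
| 10 | 30% | 28 | 44% | proceed | modify (56%) |
| 10 | 40% | 24 | 52% | proceed | do not proceed (48%) |
| 5 | 40% | 27 | 46% | proceed | modify (54%) |
| 0 | 50% | 25 | 50% | proceed | modify (50%) |

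The fifth column never changes, because f does not enter items 1 to 3.

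**The case against.** Several points on the other side are sound.

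- **Late loss is not ignored.** Item 4 records it. Section 2.12 presents all eight indicators as bearing on feasibility, and nothing says that the decision follows mechanically from items 1 to 3. A reader might infer that follow-up loss cannot affect the decision at all; the article does not support that. What stands is narrower: no threshold or action is fixed in advance.
- **The sample size is not breached.** A reader might set a 46% loss at 6 months against the 20% in section 2.13 and conclude that the pilot falls short of its own requirement. The 20% inflates a 12-week calculation, no 6-month loss rate is planned, month 6 is not named as the primary time point, and the 27 participants left in that example still exceed the calculated 26.
- **Table 1 points the other way.** It lists the drop-out row in the 6-month column, which could mean drop-out to month 6. But treatment completion and the blinding test sit in the same column, and section 2.16 places the blinding test after the final treatment session. The column therefore reads more naturally as when items are tallied. On either reading, Tables 1 and 3 need reconciling.
- **As printed, item 3 does not return a clean proceed.** A rate of 20% or less meets both the first and the last band. The illustration needs that misprint corrected first. Correcting it leaves the window at 12 weeks, so the two points are separate.
- **Descriptive items are legitimate in a pilot, and the full protocol may hold more.** True. But the bands are set out in this table, and the suggestion concerns where they stop. The Discussion's measures to keep in touch with participants and families are aimed mainly at completing treatment, and section 2.20 handles missing data in the analysis, not the progression decision.

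**Conclusion.** The point holds as a cheap improvement, not as an error that undermines the pilot. Every banded criterion in Table 3 ends with the 12-week treatment phase, and the one indicator covering 3 and 6 months is descriptive. With item 3's last band corrected, items 1 to 3 can all be satisfied at any level of loss after week 12. With 10 of 50 lost in treatment, an assumed 40% later loss gives 16 more lost, so 26/50 = 52% in total, beyond the 50% cut-off the table itself uses. The structural gap follows from reading the table; only its illustrated size rests on assumed rates. It affects the two follow-up MoCA visits and their part in the repeated-measures comparison. It does not affect the week-12 comparison, which item 3 covers.

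**What to change.** In Table 3, item 4, add a rule for the proportion of randomised participants with a MoCA at 6 months after treatment, using the cut-offs already in the table: 80% or more, proceed; 50% to below 80%, modify the protocol; below 50%, do not proceed. With 50 randomised, the boundaries are 40 and 25 participants. Keep item 3 as the separate treatment-phase rule with its last band corrected, and reconcile its stated window with the 6-month column of Table 1, for example by a note saying whether that column marks the period covered or the time of tallying.

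The cost is one line in Table 3 and one note in Table 1. The data are already collected at scheduled visits. The downside is that the pilot gains one more route to a modify or do-not-proceed result.
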